### Randomisation and blinding

Participants are randomly allocated with a 1:1 ratio into TTNS verum or TTNS sham stimulation groups, using computer-generated permuted block randomisation lists with varying block sizes. The randomisation lists are stratified according to study centre and the primary prognostic indicator, lower extremity motor score (LEMS) from the International Standards for Neurological Classification of SCI assessment.^34^ Prognostic models have shown that LEMS measured within 40 days of SCI is a reliable predictor of urinary continence and complete bladder emptying 1 year after SCI.^35^ Based on this model, LEMS cut-offs of <12, 12–37 and >37 were chosen, which correspond to a population-average estimated probability of <20%, 20%–80% and >80% for urinary continence and complete bladder emptying at 1 year after SCI.^35^ The allocation sequence and assignment of participants are centrally coordinated, and performed via the database software (Research Electronic Data Capture (REDCap)).^36 37^ To safeguard the allocation concealment, the randomisation table will be password secured and only accessible to investigators responsible for randomisation and application of the TTNS intervention.

To maintain blinding of the participants, care providers and outcome assessors, throughout the duration of the participants’ involvement in the study, the randomisation and TTNS intervention will be performed by trained operators, who are not involved in the clinical management. Additionally, the verum and sham TTNS set-ups are identical in terms of appearance, application procedure and intervention duration, and all participants receive the same information.

### Intervention

A commercially available TENS device (ELPHA II 3000, CE 0543 Certification, FH Service, Odense, Denmark) is used for both the TTNS verum and sham intervention (figure 2). The current frequency (20 Hz) and pulse width (200 μs) are preprogrammed. The current amplitude, which can be set between 0 and 100 mA, is manually adjusted for each participant during the initial setup period. Each TTNS session starts with a preparatory phase where the participant is asked to lie in a comfortable supine position and a pillow or blanket is placed on the lower part of the leg to restrict the participant’s view of their foot. Four electrodes are placed according to a prespecified order on the foot and lower leg. The first electrode is placed 4–5 cm above and 4–5 cm posterior to the medial malleolus. The next two electrodes are placed around the fifth metatarsophalangeal joint, one dorsally over the bone, and one on the plantar fat pad. A final electrode is placed distal to, and in line with, the medial malleolus in the longitudinal arch of the foot (figure 2). During an initial test period of several minutes, sensory and motor thresholds (if applicable) are assessed, current amplitudes are adjusted and the operator is carefully observing foot movement, that is, flexion or fanning of the big toe or any other motor response. The operator may reposition electrodes to optimise the electrical stimulation set-up. After the correct positioning of the electrodes has been verified by observation of the appropriate motor response,^23^ the stimulation amplitude is reduced to a submotor level, defined as 0.5–1.0 mA below the motor threshold. In the sham set-up, a cable with an interposed 1000 Ω resistance allows a current amplitude to be displayed and changed on the device without providing electrical stimulation to the participant.

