### Outcomes

The primary outcome is the occurrence of NDO jeopardising the UUT up to 12 months after SCI, that is, at 1 year after SCI or any earlier time point if NDO treatment is needed. This outcome is a composite measure including: NDO with an amplitude ≥40 cm H_2_O identified during urodynamic investigation; or else the initiation of NDO treatment with antimuscarinics and/or intradetrusor onabotulinumtoxin A injections. Urodynamics will be performed before starting TTNS (within 40 days after SCI) at follow-up visits 3 months, 6 months and 1 year after SCI, or at any earlier time point if there is reason to believe that the participant has developed NDO, before starting NDO treatment.

Secondary outcomes (table 2) were selected to further evaluate the effects of the TTNS intervention, and include clinical outcomes such as differential changes in LUT and bowel function and symptoms, sexual function, neurological function, as well as functional independence and QoL. Moreover, the evaluation of differential changes in brain and spinal cord function as well as corticospinal integrity, and biomarkers in the urine, blood, stool and bladder tissue will also provide insight into the mechanism of action underlying the TTNS intervention. All secondary outcomes may also be used to better understand the pathogenesis of NLUTD after SCI. Information collected will provide a detailed description of the disease course, and when possible, inform prognostic modelling and address causal questions. Finally, adverse events will be recorded for the duration of the participant's enrolment in the study to evaluate the safety of TTNS. Table 2 shows an overview of the secondary outcome measurement tools and assessment periods, and secondary outcome parameters are listed in detail in online supplementary 3.

10.1136/bmjopen-2020-039164.supp3Supplementary data

**Table 2 T2:** Secondary outcome measurement tools and time of assessment

Outcome and assessment tool	Assessment periods
Occurrence of neurogenic DO jeopardising the upper urinary tract over a 1-year time course (time-to-event analysis)	
Urodynamic investigation	S&B, 3M, 6M, 12M
Clinical assessment	S&B, 3M, 6M, 12M
Differential changes in lower urinary tract function	
Urodynamic investigation	S&B, 3M, 6M, 12M
Differential changes in lower urinary tract symptoms	
Bladder diary	S&B, 3M, 6M, 12M; TTNS: biweekly
International Prostate Symptom Score (IPSS)	S&B, 3M, 6M, 12M; TTNS: weekly

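### Participants with preserved leg sensation may feel verum but not sham, so their blinding is not assured and the treatment-start part of the primary outcome is open to bias

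*Protocol article*

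**What the plan says.** The Protocol article calls the trial double-blind. Under Randomisation and blinding it claims that participants, care providers and outcome assessors stay blinded for as long as the participant is in the study. It supports this by stating that "the verum and sham TTNS set-ups are identical in terms of appearance, application procedure and intervention duration", that everyone receives the same information, and that the operators take no part in clinical management.

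The Intervention section describes what each arm receives:
- At set-up, "sensory and motor thresholds (if applicable) are assessed".
- "After the correct positioning of the electrodes has been verified by observation of the appropriate motor response", "the stimulation amplitude is reduced to a submotor level, defined as 0.5–1.0 mA below the motor threshold".
- The sham cable "allows a current amplitude to be displayed and changed on the device without providing electrical stimulation to the participant".
- To mask the leg, "a pillow or blanket is placed on the lower part of the leg to restrict the participant’s view of their foot".

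Sessions last 30 minutes and take place 5 days a week for 6 to 9 weeks. Table 1 admits acute SCI at cervical or thoracic level and has no criterion on completeness or preserved sensation. For stratification, "LEMS cut-offs of <12, 12–37 and >37 were chosen".

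The Outcomes section defines the primary outcome as NDO with an amplitude of at least 40 cm H2O at urodynamic investigation, "or else the initiation of NDO treatment with antimuscarinics and/or intradetrusor onabotulinumtoxin A injections".

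**The concern.** The listed safeguards hide movement of the foot and make the apparatus look the same. None of them hides whether current is felt. A participant with preserved sensation in the stimulated leg may feel stimulation at every verum session and nothing at any sham session, over roughly 30 to 45 sessions (5 x 6 to 5 x 9).

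This matters because one route to a primary event depends on clinical judgement. A treatment start counts by itself, and extra urodynamics are prompted by suspicion that NDO has developed. Both can be influenced by what a participant reports, requests or discloses. If sensate verum participants are less often put on treatment because they believe they are being treated, the arms can differ without any difference in NDO. A positive result on the composite would then be harder to attribute to the stimulation.

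**Working it through.** **1. The text, step by step**

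| Step | Source | Status |
|---|---|---|
| Sham gives no current | Intervention | stated |
| Verum runs 0.5–1.0 mA below motor threshold | Intervention | stated |
| Some participants are expected to feel current | Intervention (sensory threshold assessed if applicable) | follows from the text |
| Preserved sensation is not excluded | Table 1 | no criterion found |
| Incomplete injuries are enrolled | Randomisation and blinding (LEMS strata up to >37) | follows; indirect evidence only, as LEMS is a motor score |
| Masking covers sight and procedure | Intervention; Randomisation and blinding | stated; sensation not named |
| A treatment start is an event without a pressure threshold | Outcomes | stated |

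**2. The plan's own figure**

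Sample size gives a sham success proportion of 0.15, a difference of 0.25, type I error 0.05, power 0.8 and a continuity correction. The two-proportion formula for 0.15 against 0.40, two-sided with correction, returns 57 per arm, 114 in total. This agrees with the article and is not disputed. The implied sham event proportion is 1 − 0.15 = 0.85.

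**3. How large the bias could be**

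The article gives none of the behavioural inputs, so these are assumptions shown as ranges:
- no true effect, and an event rate of 0.85 applied to everyone;
- share of participants who feel stimulation: s = 0.30 to 0.70;
- share of events that are treatment starts: t = 0.20 to 0.40;
- relative reduction of these starts in sensate verum participants: r = 0.30 to 0.50;
- no averted start is later captured as a urodynamic event.

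Spurious difference = 0.85 × s × t × r:
- low: 0.85 × 0.30 × 0.20 × 0.30 = 0.015
- midpoint: 0.85 × 0.50 × 0.30 × 0.40 = 0.051
- high: 0.85 × 0.70 × 0.40 × 0.50 = 0.119

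The two-sided rejection rate comes from exact binomial enumeration of the two-proportion test at 57 per arm, comparing 0.85 with 0.85 minus the spurious difference:

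| Case | Spurious difference | Uncorrected test | With continuity correction |
|---|---|---|---|
| No bias | 0 | 0.050 | 0.026 |
| Low | 0.015 | 0.057 | 0.030 |
| Midpoint | 0.051 | 0.113 | 0.067 |
| High | 0.119 | 0.353 | 0.259 |

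The midpoint is about a fifth of the planned difference (0.051 / 0.25 = 0.20). The planned analysis is logistic regression, so both test columns are approximations to it.

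**4. Sensitivity to the last assumption**

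Untreated participants still have urodynamics at the remaining visits. If half of the averted starts were later captured as events with amplitude of at least 40 cm H2O, the midpoint difference halves to 0.051 × 0.5 = 0.026 and the uncorrected rejection rate falls to 0.067.

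**The case against.** The strongest reply is that the path to bias is long. Operators are separate from clinical care, and care providers and assessors are themselves blinded. A participant would have to infer the arm, then disclose it or report differently, and a treatment decision would have to change despite the urodynamics planned before treatment. This stands as a reason for caution about size. It does not close the path, because separating the operators does not stop a participant from speaking to the treating clinician.

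A reader might infer that every sensate participant can tell the arm. The documents do not support that. LEMS does not measure foot sensation, the information leaflet is not shown, and a sham participant with impaired sensation who feels nothing need not conclude that it is sham. The inference is firmest for verum participants who feel the current. Insensate participants are unaffected. The article also does not say whether the sham cable is in place during threshold testing.

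A reader might also infer that the plan has no means of separating fewer treatment starts from less NDO. That goes too far. Table 2 lists lower urinary tract function by urodynamics as a between-arm secondary outcome at 3, 6 and 12 months, and concomitant treatment is documented for secondary analyses. What remains is narrower: the sensitivity analyses named under Statistical analyses (time-to-event and per-protocol) do not separate the components of the primary composite.

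Finally, the magnitude leans high. Averted starts may surface later as urodynamic events. Sensate participants may also have a lower event rate than 0.85, if they tend to be the less severely injured: the article links LEMS >37 to a probability above 80% of continence and complete emptying. Both objections stand.

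**Conclusion.** The point holds in limited form. Current is absent in sham and close to motor threshold in verum, sensate participants are eligible, and the masking does not address sensation. The unqualified claim of participant blinding throughout is therefore not secured for those participants. The treatment-start component of the primary outcome is exposed; the urodynamic component is much less so.

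Neither the size nor the direction of any bias can be fixed from the document. The calculated range describes a shift favouring verum. It depends wholly on the assumed sensate share, treatment-start share and behavioural shift, and should be read as upper-end for the two reasons conceded above. It shows that a modest behavioural shift could raise the false-positive rate appreciably, not that it will. Because a named sensitivity analysis would change what a positive result can support, and costs little, the change should be made.

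**What to change.** Keep the sham and the sample size.

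1. Under Statistical analyses, name as key sensitivity analysis a urodynamic-only version of the primary outcome (amplitude of at least 40 cm H2O), using the urodynamics already planned at visits and before NDO treatment. State how participants are counted whose measurement before treatment was below the threshold.
2. Under Randomisation and blinding, state that blinding is not assured in participants with preserved sensation in the stimulated leg.
3. At the end of the intervention, ask participants and treating clinicians one question each: which arm they believe was allocated.
4. Optionally, add a treatment-by-sensation analysis based on the baseline ISNCSCI assessment, labelled supportive.

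The cost is one question per person and one or two analyses of data already collected. The sensation analysis will have low power and cannot settle the matter by itself. The urodynamic-only outcome is less exposed rather than immune, since suspicion of NDO can still prompt extra investigations.

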**Figure 2 F2:**
[figure not shown]
Transcutaneous tibial nerve stimulation (TTNS) intervention. Pictures of the TTNS device, cables and electrode placements. (A) The TTNS device has two channels that can be adjusted independently. Electrodes are placed in a specified, standardised order (1–4). (B) Lateral view of the foot, showing the electrode placement on the dorsal bone and plantar fat pad of the fifth metatarsophalangeal joint. (C) Medial view of the foot, electrodes are placed 4–5 cm proximal and posterior to the medial malleolus, as well as in the longitudinal arch of the foot, distal to, and in line with, the medial malleolus.

The TTNS intervention is performed for 30 min/day, 5 days/week, starting within 40 days after SCI and ending after all 3-month follow-up assessments have been completed (total intervention period: 6–9 weeks). The majority of the participants are expected to be inpatients for the duration of the intervention, a setting that maximises participant adherence. The application of the TTNS intervention by designated and trained personnel ensures that the treatment is applied correctly while blinding is maintained. In addition, the remaining follow-up visits are part of standardised SCI care in all four participating centres, limiting the potential loss to follow-up, and ensuring that the participants receive necessary ancillary care.

Participants may be withdrawn when the study protocol is not followed, a health problem occurs with a suspected link to the stimulation, if a severe health condition/illness makes an intensive outpatient treatment or new hospitalisation necessary, consent is withdrawn, or if a pregnancy is detected. Any concomitant treatment and medication intake will be carefully documented, so that the information can be used in secondary analyses.

### Outcomes

The primary outcome is the occurrence of NDO jeopardising the UUT up to 12 months after SCI, that is, at 1 year after SCI or any earlier time point if NDO treatment is needed. This outcome is a composite measure including: NDO with an amplitude ≥40 cm H_2_O identified during urodynamic investigation; or else the initiation of NDO treatment with antimuscarinics and/or intradetrusor onabotulinumtoxin A injections. Urodynamics will be performed before starting TTNS (within 40 days after SCI) at follow-up visits 3 months, 6 months and 1 year after SCI, or at any earlier time point if there is reason to believe that the participant has developed NDO, before starting NDO treatment.

Secondary outcomes (table 2) were selected to further evaluate the effects of the TTNS intervention, and include clinical outcomes such as differential changes in LUT and bowel function and symptoms, sexual function, neurological function, as well as functional independence and QoL. Moreover, the evaluation of differential changes in brain and spinal cord function as well as corticospinal integrity, and biomarkers in the urine, blood, stool and bladder tissue will also provide insight into the mechanism of action underlying the TTNS intervention. All secondary outcomes may also be used to better understand the pathogenesis of NLUTD after SCI. Information collected will provide a detailed description of the disease course, and when possible, inform prognostic modelling and address causal questions. Finally, adverse events will be recorded for the duration of the participant's enrolment in the study to evaluate the safety of TTNS. Table 2 shows an overview of the secondary outcome measurement tools and assessment periods, and secondary outcome parameters are listed in detail in online supplementary 3.

10.1136/bmjopen-2020-039164.supp3Supplementary data

**Table 2 T2:** Secondary outcome measurement tools and time of assessment

Outcome and assessment tool	Assessment periods
Occurrence of neurogenic DO jeopardising the upper urinary tract over a 1-year time course (time-to-event analysis)	
Urodynamic investigation	S&B, 3M, 6M, 12M
Clinical assessment	S&B, 3M, 6M, 12M
Differential changes in lower urinary tract function	
Urodynamic investigation	S&B, 3M, 6M, 12M
Differential changes in lower urinary tract symptoms	
Bladder diary	S&B, 3M, 6M, 12M; TTNS: biweekly
International Prostate Symptom Score (IPSS)	S&B, 3M, 6M, 12M; TTNS: weekly
Urinary Symptom Profile (USP)	S&B, 3M, 6M, 12M; TTNS: weekly
Differential changes in neurological structure and function	
Neurourological physical examination	S&B, 3M, 6M, 12M
International Standards for Neurological Classification of Spinal Cord Injury (ISNCSCI) assessment	S&B, 3M, 6M, 12M
Nerve conduction studies (NCS)	S&B, 3M, 6M, 12M
Electromyography (EMG)	S&B, 3M, 6M, 12M
Electroencephalography (EEG)	S&B, 3M, 6M, 12M
Transcranial magnetic stimulation (TMS)	S&B, 3M, 6M, 12M
Magnetic resonance imaging (MRI)	S&B, 3M, 6M, 12M
Differential changes in bowel and pelvic floor function	
Rectal sensitivity examination	S&B, 3M, 6M, 12M
Anorectal manometry	S&B, 3M, 6M, 12M
Barostat assessment	S&B, 3M, 6M, 12M
Differential changes in bowel symptoms	
Bowel diary	S&B, 3M, 6M, 12M; TTNS: biweekly
Neurogenic Bowel Dysfunction Score (NBD)	S&B, 3M, 6M, 12M; TTNS: weekly
Differential changes in sexual function	
Female Sexual Function Index (FSFI)	S&B, 3M, 6M, 12M
International Index of Erectile Function (IIEF)	S&B, 3M, 6M, 12M
Clinical assessment	S&B, 3M, 6M, 12M
Differential changes in spasticity	
Modified Ashworth Scale (MAS)	S&B, 3M, 6M, 12M
Spinal Cord Injury (SCI) Spasticity Evaluation Tool (SCI-SET)	S&B, 3M, 6M, 12M; TTNS: weekly
Differential changes in functional independence	
Spinal Cord Independence Measure (SCIM) III	S&B, 3M, 6M, 12M
Differential changes in quality of life	
International Prostate Symptom Score (IPSS)	S&B, 3M, 6M, 12M; TTNS: weekly
Qualiveen	S&B, 3M, 6M, 12M; TTNS: weekly
Differential changes in biochemical and molecular biomarkers in the urine, blood and stool, as well as in the bladder tissue	
Histomorphology	S&B 6M
Enzyme-linked immunosorbent assay (ELISA)	S&B, 3M, 6M, 12M
Western immunoblotting	S&B, 3M, 6M, 12M
Reverse transcription polymerase chain reaction (RT-PCR)	S&B, 3M, 6M, 12M
Microbiome analysis	S&B, 3M, 6M, 12M
Safety of TTNS	
Adverse events and serious adverse events as assessed by clinical record check and patient interview	Any time

Assessment periods are referenced to the date of SCI diagnosis and include: screening and baseline (S&B; days 5–39), 3-month follow-up (3M; days 91±10), 6-month follow-up (6M; days 182±10) and 12-month follow-up (12M; days 365±10). Additionally, some surveys are administered weekly during the transcutaneous tibial nerve stimulation (TTNS) treatment period (TTNS: weekly), and the bowel and bladder diaries are administered once every 2 weeks during the treatment period (TTNS: biweekly).

DO, detrusor overactivity.

Generally, the outcome assessments are administered at screening and baseline as well as during each of the three follow-up visits (figure 1). One notable exception is the bladder biopsy, which will take place at baseline and the 6-month follow-up visit, and only with additional consent. Moreover, during the intervention period, participants will complete some of the questionnaires once per week, and the bladder and bowel diaries once every 2 weeks. Withdrawal from the study can occur at any time if treatment for NDO is indicated. If withdrawal occurs, all study completion assessments should be performed whenever possible. Furthermore, the trial is nested in the SwiSCI cohort study, so observation of the participants will continue through the cohort study after the end of TASCI. SwiSCI can provide long-term, open-label outcome data regarding morbidity, activities and participation (eg, labour market participation), QoL and life expectancy.

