Age ≥ 18 years Patients with acute SCI (traumatic SCI and sudden onset (<7 days) non-traumatic SCI), within 40 days after injury Patients with acute SCI at cervical or thoracic level Willingness to take part and follow the requirements of the protocol during TASCI (up to 1 year after SCI): No percutaneous tibial nerve stimulation No functional electrical stimulation (FES) apart from upper limb FES No electrical muscle stimulation Informed consent	Contraindications to the investigational product Treatment with antimuscarinics or mirabegron DO with contractions greater than 40 cm H_2_O at a bladder filling volume of less than 500 mL at baseline visit Known or suspected non-adherence, drug or alcohol abuse Inability to follow the procedures of the study, for example, due to language problems, psychological disorders, dementia, and so on, of the participant Participation in another study with investigational drug or product within the 30 days preceding and during the present study Neuromodulation treatment for urological or bowel indication in the last 6 months or ongoing Botulinum toxin injections in the detrusor and/or urethral sphincter in the last six months Bilaterally absent tibial nerve compound muscle action potential (amplitude < 1 mV) Women who are pregnant or breast feeding Individuals especially in need of protection (according to Research with Human Subjects published by the Swiss Academy of Medical Sciences (www.samw.ch/en/News/News.html) Enrolment of the investigator, their family members, employees and other dependent persons Pre-existing or concomitant medical condition apart from SCI that might pose a safety issue or would interfere with interpretation of study results or study conduct (eg, Parkinson’s disease, neurodegenerative disorders including multiple sclerosis and amyotrophic lateral sclerosis, urological malignancies)

Urinary tract infection (UTI) is a transitory exclusion criterion for all functional assessments, including urodynamics. Before undergoing functional assessments, participants are screened for UTIs and haematuria. If a UTI is identified, treatment is initiated, and the functional assessments are rescheduled once the participant has been symptom free for at least 3 days.

DO, detrusor overactivity; SCI, spinal cord injury.

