### Sample size

Presuming a proportion of spontaneous success among the sham group of 0.15,^23^ 114 participants (57 verum, 57 sham) need to be included to detect a difference of 0.25 in the proportion of participants who develop NDO, and thereby to correctly reject the null hypothesis with a probability (power) of 0.8. The type I error probability associated with the test of this null hypothesis is 0.05. Since the primary outcome variable is binary, this sample size analysis included a continuity correction to avoid type I error inflation.

Using prospective data collected by the SwiSCI inception cohort for the years 2014–2016 and applying a modified version of the TASCI inclusion/exclusion criteria, a total of 193 eligible patients are predicted during the 3-year recruitment period of TASCI. Anticipating a recruitment rate of 66%, this implies that the requisite 114 participants can be included within 3 years. Expected participant numbers per centre during the study period are 20 for Basel, 42 for Nottwil, 13 for Sion and 39 for Zürich. Moreover, these data imply that participants who withdraw or drop out can be replaced.

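### The treatment part of the primary outcome leaves out mirabegron, so a narrow group treated for NDO is scored by which drug was started; the trigger wording also needs aligning

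*Protocol article*

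**What the plan says.** All references are to the protocol article.

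- **Outcomes, primary outcome.** The event can occur "at 1 year after SCI or any earlier time point if NDO treatment is needed". It has two components. The first is an NDO amplitude of 40 cm H2O or more "identified during urodynamic investigation". The second is "or else the initiation of NDO treatment with antimuscarinics and/or intradetrusor onabotulinumtoxin A injections".
- **Outcomes, same paragraph.** Besides the scheduled visits, urodynamics are to be done earlier "if there is reason to believe that the participant has developed NDO, before starting NDO treatment".
- **Participants, Table 1.** One exclusion criterion reads "Treatment with antimuscarinics or mirabegron". The commitments that participants make for the year after injury concern electrical stimulation methods. They do not mention drugs.
- **Outcomes, text after Table 2.** "Withdrawal from the study can occur at any time if treatment for NDO is indicated". Completion assessments are then to be done where possible, and observation continues in the SwiSCI cohort.
- **Intervention.** "Any concomitant treatment and medication intake will be carefully documented, so that the information can be used in secondary analyses".

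**The concern.** The entry criteria put antimuscarinics and mirabegron on the same footing: either makes a patient ineligible. The outcome definition does not. It names specific treatments, with no wording such as *for example*, and mirabegron is not among them. Two participants with the same bladder findings, both put on a drug for NDO, can therefore receive opposite primary outcomes solely because of the drug chosen.

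The trigger for the treatment component is a second, separate matter. *Needed*, *initiation* and *indicated* pick out slightly different people. They part company for someone who is judged to require treatment but leaves the study before starting it.

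At stake is whether the primary outcome can be determined for every participant by one rule. If prescribing differed between arms or centres, the comparison would partly reflect prescribing.

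**Working it through.** **1. Apply the listed components case by case** (amplitudes in cm H2O).

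| Case | Before treatment | Started for NDO | At 12 months | Score by the listed components |
|---|---|---|---|---|
| A | ≥40 | any drug | any | event |
| B | <40 | antimuscarinic | <40 | event |
| C | <40 | mirabegron | <40 | non-event |
| D | not measured | mirabegron | <40 | non-event |
| E | <40 | mirabegron | ≥40 | event |
| F | <40 | nothing before withdrawal; listed drug later | not observed | depends on whether the later start is captured |

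B and C differ only in the drug and are scored in opposite ways. The mirabegron gap is confined to C and D. Case A is protected by the rule that urodynamics precede NDO treatment. Case F comes from the trigger wording and has nothing to do with mirabegron or with a drug masking NDO.

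**2. Reproduce the planned sample size.** Inputs from Sample size: "Presuming a proportion of spontaneous success among the sham group of 0.15", a difference of 0.25, power 0.8, type I error 0.05, continuity correction. The event proportions are 1 − 0.15 = 0.85 in sham and 0.85 − 0.25 = 0.60 in verum, with mean 0.725. Sidedness is not stated; I take it as two-sided.

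- Uncorrected: n₀ = [1.960·√(2·0.725·0.275) + 0.842·√(0.85·0.15 + 0.60·0.40)]² / 0.25² = 48.88 per arm.
- Corrected: n = (n₀/4)·[1 + √(1 + 4/(n₀·0.25))]² = 56.6, rounded up to 57 per arm, or 114 in total.

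This matches the plan. No planned figure is wrong.

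**3. Illustration of what misscoring would do.** Let m be the share of true events scored as non-events. **The document gives no value for m; every m below is an assumption.** If m is equal in both arms, the proportions become 0.85(1 − m) and 0.60(1 − m), and the difference is 0.25(1 − m). Exact power of the continuity-corrected test at 57 per arm:

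| m, both arms | Sham | Verum | Difference | Power |
|---|---|---|---|---|
| 0 | 0.850 | 0.600 | 0.250 | 0.808 |
| 2% | 0.833 | 0.588 | 0.245 | 0.778 |
| 5% | 0.8075 | 0.570 | 0.2375 | 0.732 |
| 10% | 0.765 | 0.540 | 0.225 | 0.651 |
| 20% | 0.680 | 0.480 | 0.200 | 0.500 |

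If m = 5% in one arm only:

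- sham only: 0.85·0.95 − 0.60 = 0.2075, power 0.612;
- verum only: 0.85 − 0.60·0.95 = 0.28, power 0.887.

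The sign of the effect depends on where the misscoring falls, and the document does not settle that. Since only cases C and D contribute to the mirabegron gap, the larger values of m would need a large share of all events to be of those two kinds. Nothing in the article suggests this.

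**The case against.** **The pre-treatment rule already deals with most of it.** Starting a drug for NDO presupposes a reason to suspect NDO, which calls for urodynamics first. This stands. It removes every participant at 40 or above before treatment and leaves only cases C and D. A reader might infer that drug-masked NDO will generally be counted as success; the document does not support that.

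**The list has a rationale.** The Introduction names antimuscarinics and onabotulinumtoxin A as first-line and second-line treatment, and the outcome mirrors them. An entry exclusion serves a clean baseline and need not match the outcome list. This is a fair account of how the list arose, but it does not remove the opposite scoring of B and C.

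**The phrase about treatment being needed could cover mirabegron.** Read broadly, yes. But the next sentence defines the composite by named treatments, so two careful readers could score case C differently. That is a reason to clarify.

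**The trigger words do different jobs.** *Needed* sets the timing, *initiation* is the operating rule, and *indicated* governs withdrawal. This largely stands: they are not three rival definitions. What remains is case F. Neither the completion assessments nor the cohort follow-up guarantees that a later start of treatment is scored.

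**Counting treatment started below 40 as jeopardising the upper urinary tract is itself debatable.** One might be tempted to add this as a further fault. It pulls the other way: if such treatment should not count, most of the mirabegron gap disappears. It is therefore not pressed here; a supportive analysis on amplitude alone would inform it.

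**Conclusion.** The point holds in a limited form. By the written rule, a participant started on mirabegron for NDO with an amplitude below 40 before treatment (or none measured) and below 40 at 12 months is a non-event, while the same participant on an antimuscarinic is an event. Separately, the mixed trigger wording leaves it open whether treatment started after withdrawal is scored.

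The size is unknown. The document gives no expected mirabegron use, and the affected group is narrow. A reader might infer from the equal-arm table that the trial is underpowered or biased towards no effect. That does not follow: m is assumed, and misscoring in verum alone would enlarge the apparent difference. The sample size of 114 stands.

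Severity is minor to moderate. The reason to act is that the primary outcome should give one answer per participant. The conclusion rests on reading the treatment list as closed and on the article alone; the full protocol is not shown and may already settle it.

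**What to change.** Reconcile Table 1, the primary outcome definition and the withdrawal sentence, for scoring purposes only and before unblinding:

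1. Define the treatment component as initiation of any drug or injection treatment given for NDO, naming mirabegron.
2. Use one trigger word, *initiation*, wherever the outcome is described, and keep the withdrawal wording clearly apart from it.
3. Score initiation up to day 365 also after withdrawal, from the concomitant medication record and, where available, cohort follow-up. State that this record feeds the primary outcome as well as secondary analyses.
4. Optionally, add a supportive analysis on urodynamic amplitude alone, using the last urodynamics before treatment.

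This changes how outcomes are scored, not who is treated or with what. The cost is slightly broader outcome wording, a check of medication after withdrawal, and one small extra analysis. The planned sample size does not change.
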